## Abstract

**Introduction:** Rheumatoid arthritis (RA) is an autoimmune disease characterized by progressive bone erosion on diarthrodial joints. RA patients usually experienced three stages before final diagnosis: the health period, the pre-clinical period (immune response exists without clinical symptoms), and the pre-RA period (immune response exists with mild inflammatory manifestation). Presently, there is seldom guidance referring to early intervention which is a benefit for stable disease conditions and low morbidity. Prophylactic treatment is a major feature of traditional Chinese medicine (TCM). In this present study, a multi-center, double-blind, placebo-controlled clinical trial is carried out to evaluate both efficacy and safety in preventing RA progression on Yunpi Qufeng Chushi formula (YQCF).

**Method:** The multi-center, double-blind, placebo-controlled clinical trial is conducted in 13 hospitals nationwide. A total of 390 patients ages between 18 and 70 will be recruited in the trial. They will be randomly assigned to the intervention group (YQCF) and placebo group. The follow-up visit will be taken every 3 months from baseline to 1 year. Diagnosis, disease activity scores, clinical disease activity index (CDAI), simplified disease activity index (SDAI), TCM syndrome scores, and safety assessments will be recorded at every visit. Joint color doppler ultrasound, health assessment questionnaire-disability index (HAQ-DI), and functional assessment of chronic illness therapy-fatigue (FACIT-F) will be recorded at baseline and the last visit.

**Discussion:** This work will provide evidence of YQCF in preventing RA progression. However, whether early intervention would benefit the controlling RA disease still needs a long-term follow-up.

**Ethics and dissemination:** Protocol version 2 (201910-1). This research was approved by the medical ethics committee of Zhejiang Chinese Medical University (2019-045). Results will be published in a peer-reviewed academic journal.

**Trial registration numbers:**
http://www.chictr.org.cn/index.aspx, ChiCTR1900024166.

## 1 Introduction

Rheumatoid arthritis (RA) is an autoimmune disease characterized by progressive bone erosion on diarthrodial joints. The global incidence of RA is about 0.5–1% (Firestein et al., 2020). Although the pathogenesis of RA is not fully understood, genes, infection, and the environment have been demonstrated to be involved. RA patients usually experienced three stages before final diagnosis, namely the health period, the pre-clinical period (immune response exists without clinical symptoms), and the pre-RA period (immune response exists with mild inflammatory manifestation), and sometimes making a definite diagnosis is time-consuming (Smolen et al., 2018).

RA management emphasized the early diagnosis and targeted therapy (Aletaha and Smolen, 2018; Smolen et al., 2018) which can slow down disease progression and avoid irreversible disability. However, there is little guidance to make the detailed suggestion for pre-clinical and pre-RA patients (Fraenkel et al., 2021). To date, many trials have tried to answer the definition and management of pre-clinical RA and pre-RA (Lard et al., 2001; Nell et al., 2004; van Dongen et al., 2007; Lukas et al., 2011; Wevers-de Boer et al., 2012; van Aken et al., 2014; Stamm et al., 2018; Gerlag et al., 2019). For example, van Dongen et al. (2007) found that MTX was beneficial in postponing the diagnosis of RA (ACR 1987 criteria), and retarding radiographic joint damage in undifferentiated arthritis (UA) patients. Lukas et al. (2011) showed that early initiation of DMARD therapy reduces the radiological progression of 12 months. In all, the decision supported that pre-RA or pre-clinical RA patients benefit from early initiation of DMARD.

Prophylactic treatment is a major feature of traditional Chinese medicine (TCM). In the recent pandemic of SARS-Cov-2, the combination of Western medicine and TCM had better performance on preventing disease transformation than Western medicine only (Li et al., 2020; Wu et al., 2021). To date, there is no TCM-related trial aimed at preventing RA onset. Non-specific musculoskeletal (MSK) symptoms with positive anticyclic citrullinated peptide (anti-CCP) antibodies patients have a high risk of developing into RA in 12 months (Rakieh et al., 2015). Besides, some anti-CCP negative arthralgia patients also have a high risk of developing RA (van Steenbergen et al., 2017). Thus, we would conduct a multi-center, double-blind, placebo-controlled randomized trial recruiting both anti-CCP positive and negative patients, to demonstrate the efficacy and safety of Yunpi Qufeng Chushi formula (YQCF) in preventing the development of RA.

## 2 Materials and Methods

### 2.1 Study Setting

The multi-center, double-blind, placebo-controlled clinical trial is conducted in 13 hospitals nationwide including First Affiliated Hospital of Zhejiang Chinese Medical University, Second Affiliated Hospital of Zhejiang Chinese Medical University, Third Affiliated Hospital of Zhejiang Chinese Medical University, Xiyuan Hospital of China Academy of Chinese Medical Sciences, Guanganmen Hospital of China Academy of Chinese Medical Sciences, Dongfang Hospital of Beijing University of Chinese Medicine, China-Japan Friendship Hospital, Shanghai Hospital of Traditional Chinese Medicine, First Affiliated Hospital of Zhejiang University School of Medicine, Second Affiliated Hospital of Zhejiang University School of Medicine, Sir Run Shaw Hospital of Zhejiang University School of Medicine, First Affiliated Hospital of Guangzhou University of Traditional Chinese Medicine, and First Affiliated Hospital of Anhui University of Chinese Medicine.

### 2.2 Participants

A total of 390 participants aged 18–70 will be recruited. Inclusion and exclusion criteria are presented as follows.

To date, the definition (or criteria) of pre-RA is controversial. We propose our definition based on the trials mentioned above. For the patients with positive anti-CCP antibodies: at least 1 joint involvement (any swollen or tender joint on examination) and do not meet any RA classification criteria [ACR 1987 revised criteria (Arnett et al., 1988) and ACR/EULAR 2010 criteria (Aletaha et al., 2010)]. For the patients with negative anti-CCP antibodies: meet with at least 5 parameters according to the EULAR definition of arthralgia suspicious for progression to RA (van Steenbergen et al., 2017) (details available in Table 1).

**TABLE 1 T1:** EULAR defined characteristics describing arthralgia at risk for RA (adapted from van Steenbergen et al., 2017).

History taking
1. Joint symptoms of recent onset (duration <1 year)
2. Symptoms located in MCP joints
3. Duration of morning stiffness ≥60 min
4. Most severe symptoms present in the early morning
5. Presence of a first-degree relative with RA
Physical examination:
6. Difficulty with making a fist
7. Positive squeeze test of MCP joints

### 2.3 Inclusion Criteria

(1) Meet the definition which we proposed of pre-RA.(2) The course of disease is between 6 weeks and 6 months.(3) Meet with the diagnostic criteria of TCM syndrome of spleen deficiency and wind-damp blockade syndrome (available in Table 2).(4) The men and women patients are aged 18–70 years.(5) Patients provided with informed consent and signed agreement.

**TABLE 2 T2:** Diagnostic criteria of spleen deficiency and wind-damp blockade syndrome.

Primary symptoms and signs	(1) Joint stiffness
	(2) Joint wandering pain
	(3) >1 joint pain
	(4) Epigastric distention
Secondary symptoms and signs	(1) Heavy body and limbs
	(2) Loose stool
	(3) Loss of appetite
	(4) Tongue condition: pale tongue with white coating
	(5) Pulse condition: thin and soft pulse

Patients with four primary symptoms or three primary symptoms and two or more secondary symptoms could be diagnosed as spleen deficiency and wind-damp blockade syndrome.

### 2.4 Exclusion Criteria

(1) Any DMARDs, including conventional synthetic DMARDs (csDMARDs), targeted synthetic DMARDs (tsDMARDs), and biological DMARDs (bDMARDs), have been used for treatment within 2 months before enrollment. Further explanation: a patient is undertaking some DMARDs and is willing to take part in the study, they can stop the DMARDs for 2 months and subsequently recheck the necessary examination to take part in the trial.(2) Patients have recently taken glucocorticoids, such as prednisone.(3) With a history of severe organ diseases or mental diseases.(4) Patients are allergic to the drugs involved in the study protocol or have contraindications.

### 2.5 Interventions

Subjects will be randomly allocated to either the intervention group or the control group through a central randomization system. Treatment will continue for 48 weeks. The visit time will be set at 0 weeks (recruitment), 12, 24, and 48 weeks. YQCF granules and the placebo granules were manufactured by China Resources Sanjiu Pharmaceutical Co., Ltd. One day dosage of YQCF granules: Atractylodis rhizoma [Asteraceae; Atractylodes lancea (Thunb.) DC.]: 2.5 g (equally 15 g herb medicine, abbreviated as 15 g), Aaposhnikoviae radix [Apiaceae; Saposhnikovia divaricata (Turcz. ex Ledeb.) Schischk.]: 0.3 g (6 g), Schizonepetae herba [Lamiaceae; Nepeta tenuifolia Benth.]: 1.2 g (12 g), Sinomenii caulis [Menispermaceae; Sinomenium acutum (Thunb.) Rehder and E.H.Wilson]: 2 g (15 g), Lonicerae japonicae flos [Caprifoliaceae; *Lonicera japonica* Thunb.]: 3 g (15 g), Smilacis glabrae rhizoma [Smilacaceae; Smilax glabra Roxb.]: 1.33 g (20 g), Cynanchi paniculati radix et rhizoma [Apocynaceae; Vincetoxicum mukdenense Kitag.]: 2 g (12 g), Coicis semen [Poaceae; Coix lacryma-jobi var. ma-yuen (Rom. Caill.) Stapf]: 1.5 g (15 g), and Glycyrrhizae radix et rhizoma [Fabaceae; Glycyrrhiza glabra L.]: 2 g (6 g). Drug compatibility: 1) joint significantly swelling and pain: Leigongteng [Celastraceae; Tripterygium wilfordii Hook. f.]: 1.5 g (15 g), cuscutae semen [Convolvulaceae; Cuscuta chinensis Lam.]: 0.75 g (15 g), Polygoni cuspidati rhizoma et radix [Polygonaceae; Reynoutria japonica Houtt.]: 1 g (15 g); 2) exuberant heat: Anemarrhenae rhizoma [Asparagaceae; Anemarrhena asphodeloides Bunge]: 0.75 g (15 g); 3) exuberant cold: Cinnamomi ramulus [Lauraceae; Neolitsea cassia (L.) Kosterm.]: 1.25 g (15 g); 4) low back pain: Eucommiae cortex [Eucommiaceae; Eucommia ulmoides Oliv.]: 0.6 g (12 g); 5) pain above the waist: Mori ramulus [Apiaceae; Hansenia weberbaueriana (Fedde ex H. Wolff) Pimenov and Kljuykov]: 0.9 g (18 g); 6) pain below the waist: Cyathulae radix [Apiaceae; Angelica biserrata (R.H. Shan and C.Q. Yuan) C.Q. Yuan and R.H. Shan]: 1.49 g (10 g). The YQCF granules and placebo will be packed into identical-looking medicine bags. Dosage: two bags per day. Our research group published a study on the identification of the main components of YQCF by liquid chromatography–mass spectrometry. The methods and the results were available at Li et al. (2021). Besides, we also applied quality control using HPLC, the methods and the results are available in Supplementary Material S5. The quality control data provided by China Resources Sanjiu Pharmaceutical Co., Ltd. are available in Supplementary Material S6.

Nonsteroidal anti-inflammatory drugs (NSAIDs) will be allowed to be prescribed when the patients suffer from pain. DAMARs and glucocorticoids will not be allowed in the study. The untaken drug will be returned.

Mild and moderate adverse events (AEs) will change the composition of YQCF granules according to the relative granules AEs. For example, Sinomenium acutum (Thunb.) Rehder and E.H. Wilson will be removed because it would cause cutaneous pruritus. Severe AEs will stop the intervention and the patient will withdraw.

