### 2.6 Outcomes

#### 2.6.1 Primary Outcomes

##### 2.6.1.1 RA Transition Rate

Definition: pre-RA patients who fulfill any criteria of RA classification at any time will be defined as “RA transition.” Survival time will be recorded as the number of days between the date of informed consent and the date of transition.

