### 2.8 Sample Size

Based on the primary outcome, we use the model of “tests for two proportions” in PASS 15.0. Alternative hypothesis: two-sided. Test type: Z-test (unpooled). Power was set at 0.9 and alpha was set at 0.05. The intervention group and control group were allocated a 1:1 ratio. The effect size of the treatment group (P1): based on the results of our former small sample of observational study (results unpublished), about 53.26% of patients would transit to RA after 1 year of TCM treatment. The effect size of the control group (P2): without any medication interventions, about 70% of early-stage UA patients with ACPAs meet the 1987 ACR criteria 1-year follow-up (Firestein et al., 2016). We would need 173 subjects in each group. Predicting a 10% dropout rate, the subjects rise to 385. Considering there were 13 centers that took part in the studies, the final subject was set at 390 (30 subjects per center).

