### 2.12 Statistical Methods

#### 2.12.1 Primary Outcome

The final RA transition rate will be performed by Pearson’s chi-square or Fisher’s exact chi-square tests. In addition, RA transition survival analysis will be performed by Kaplan-Meier survival analysis. Binary logistic regression is utilized to investigate the multiple variables which can affect RA transition rate. The variables include sex, age, anti-ccp and RF state, family history, DAS28, continuous NSAIDs use, and YQCF use. Per-protocol (PP) analysis and intention-to-treat (ITT) analysis will be applied in chi-square tests, survival analysis, and binary logistic regression.

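### Section 2.5 withdraws patients after a severe adverse event and provides for no later RA assessment, although an ITT analysis of 48-week RA transition is promised

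*Protocol article*

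**What the plan says.** All places are in the protocol article.

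- Section 2.5 (Interventions), on adverse events: "Severe AEs will stop the intervention and the patient will withdraw". The sentence names two consequences, one for the treatment and one for the patient. The same section sets the planned duration: "Treatment will continue for 48 weeks".
- Section 2.6.1.1 defines the primary outcome with no restriction to time on treatment: "pre-RA patients who fulfill any criteria of RA classification at any time will be defined as" RA transition. Table 3 schedules the evaluation of RA conversion at weeks 4, 12, 24 and 48.
- Section 2.12.1: "The final RA transition rate will be performed by Pearson’s chi-square or Fisher’s exact chi-square tests". Kaplan-Meier and logistic analyses are added, and "Per-protocol (PP) analysis and intention-to-treat (ITT) analysis will be applied in chi-square tests, survival analysis, and binary logistic regression".
- Section 2.8 allows for loss in the number recruited: "Predicting a 10% dropout rate, the subjects rise to 385".
- Section 2.13 describes the adverse events as mild. No rate of severe events is given anywhere.

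**The concern.** Stopping the granules is already stated, so the natural reading of the second half of the section 2.5 sentence is that the patient leaves the trial. A patient withdrawn at week 6 would have had the week 4 evaluation of RA conversion but not those at weeks 12, 24 and 48. An ITT comparison of the final transition rate still has to place that patient somewhere.

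Two features make this more than ordinary dropout. First, the trigger is an adverse event, and the active granules can cause adverse events. Section 2.5 itself names a component expected to cause itching. The number withdrawn could therefore differ between arms. Second, whether follow-up continues is a rule of trial conduct. An analysis plan can choose how to handle missing outcomes, but it cannot recover assessments that sites were told not to make.

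What is at stake is the size, and in an unfavourable case the credibility, of the primary ITT comparison.

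**Working it through.** **Step 1: the plan's own sample size.** Section 2.8 gives p1 = 0.5326 (YQCF), p2 = 0.70 (control), a two-sided unpooled Z-test, 1:1 allocation, and "Power was set at 0.9 and alpha was set at 0.05".

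n per arm = (1.960 + 1.282)² × [0.5326 × 0.4674 + 0.70 × 0.30] / (0.70 − 0.5326)² = 172.08, rounded up to 173. Then 2 × 173 / 0.9 = 384.4, rounded up to 385. Both stated figures reproduce, and nothing below depends on an error there. The final 390 gives 195 per arm. The planned difference is 70 − 53.26 = 16.74 points.

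**Step 2: the passages side by side.** Section 2.5 ends the patient's participation after a severe AE. Section 2.6.1.1 counts a transition at any time, section 2.12.1 promises ITT, and Table 3 places three of its four RA-conversion evaluations at week 12 or later. No section says that these evaluations continue after a withdrawal.

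**Step 3: possible size.** The withdrawal rates are assumptions, because the document gives none. Let w be the share withdrawn in an arm. Take a true risk of 70% in both arms (no effect) and suppose that nobody had transitioned before withdrawal.

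- *Counted as non-transitions:* observed rate = 0.70 × (1 − w), so spurious benefit = 0.70 × (w_YQCF − w_placebo). Rejection is the two-sided 5% rate of the unpooled Z-test with 195 per arm, by normal approximation.
- *Excluded:* observed rate = (0.70 − w × r) / (1 − w), where r is the true risk among the withdrawn, taken from 50% to 90%.
- *Counted as transitions:* observed rate = 0.70 × (1 − w) + w = 0.70 + 0.30w, so the shift is 0.30 × (w_YQCF − w_placebo) against YQCF.

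| Withdrawn, YQCF / placebo | Non-transitions: observed rates | Spurious benefit (points) | Rejection | Excluded: bias (points) | Transitions: shift (points) |
|---|---|---|---|---|---|
| 2% / 1% | 68.6% / 69.3% | 0.7 | 5.3% | within about ±0.2 | −0.3 |
| 5% / 2% | 66.5% / 68.6% | 2.1 | 7.3% | within about ±0.6 | −0.9 |
| 10% / 2% | 63.0% / 68.6% | 5.6 | 21.5% | within about ±1.8 | −2.4 |

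With exclusion, the bias is zero if the withdrawn have the same 70% risk as everyone else.

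**Step 4: bounds around the planned effect.** Take the design rates among patients who stay, and give the withdrawn the least and then the most favourable outcomes for YQCF. At 2% / 1%, the lower bound is 0.70 × 0.99 − (0.5326 × 0.98 + 0.02) = 0.151 and the upper bound is (0.70 × 0.99 + 0.01) − 0.5326 × 0.98 = 0.181. By the same formulas, the difference lies between 13.0 and 20.0 points at 5% / 2%, and between 10.7 and 22.7 points at 10% / 2%.

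**The case against.** The strongest reply is that this is one condensed sentence in a journal article. It does not say that data collection ends. Table 3 has a row for suspension standards at visits 2 to 5, so fuller rules may exist in the full protocol, and section 2.11 plans measures to support complete follow-up. Adverse events are expected to be mild, so few patients may be affected. At 2% versus 1% withdrawn the distortion is negligible. Kaplan-Meier under ITT is already planned and uses follow-up up to withdrawal.

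Much of this stands. Reading withdrawal as leaving the study is natural but not expressly stated, and the effect is small if severe events are rare. Two parts do not answer the point. The sentence as written instructs sites, and nothing shown limits it. Kaplan-Meier censoring at an AE-triggered withdrawal assumes that the censoring is non-informative, which is exactly what is in doubt.

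A reader might also go further than the document allows:

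- *That these patients' primary outcome is lost altogether and ITT cannot be unbiased.* A transition seen before withdrawal counts. Bias depends on how many withdraw, the imbalance between arms, their risk and the missing-data method.
- *That the chi-square test must either drop them or count them as non-transitions.* Imputation, or counting them as transitions, is equally possible. The article fixes no rule, and an analysis plan commonly does.
- *That the 10% allowance makes this a completers analysis, or that all dropouts will count as non-events and reduce power.* Inflating recruitment protects precision and does not define the analysis set. Section 2.8 does not attribute the 10% to severe AEs.
- *That the loss depends on the outcome.* Nothing in the document links severe AEs to the risk of RA transition.

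**Conclusion.** The point holds as a conflict between a conduct rule and the promised analysis. Following section 2.5 as written leaves RA status unobserved after withdrawal for patients with a severe AE. Since the loss may differ between arms, the ITT result for them would rest on assumptions that the data cannot check.

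The size cannot be settled from the document. Under the stated assumptions it runs from negligible (0.7 points) to about a third of the planned effect (5.6 / 16.7 = 0.34). The upper figure requires frequent and clearly unequal severe AEs, which section 2.13 does not lead one to expect, and a non-transition rule that the article does not contain. Exclusion gives smaller figures. The case for changing the text rests on how cheaply the uncertainty can be avoided; the document does not show that serious bias will occur.

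**What to change.** Reconcile sections 2.5 and 2.12.1 by separating two events: stopping the granules and leaving the study. State that the RA-conversion assessments already scheduled in Table 3 continue to week 48 for every randomised patient, whatever happens to treatment, unless the patient withdraws consent. When treatment should stop is a clinical matter on which this point takes no position.

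For patients still lost, add a sensitivity analysis of the ITT comparison, for example counting them as transitions. The planned chi-square test and the sample size need no change.

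The cost is a sentence in the protocol, one extra analysis, and a few already-scheduled visits for patients who are off treatment.

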### 2.6 Outcomes

#### 2.6.1 Primary Outcomes

##### 2.6.1.1 RA Transition Rate

Definition: pre-RA patients who fulfill any criteria of RA classification at any time will be defined as “RA transition.” Survival time will be recorded as the number of days between the date of informed consent and the date of transition.

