### 2.7 Participant Timeline

The study will last 3 years: from July 2019 to July 2022. The timeline and study procedure are available in Table 3 and Figure 1.

**TABLE 3 T3:** Study procedure table.

Visit Project	Screen period (baseline)		Visit			
	1		2	3	4	5
Time of visit	−4 weeks-0 days	0 ± 2 days	4 weeks ± 2 days	12 weeks ± 3 days	24 weeks ± 5 days	48 weeks ± 5 days
General information	●					
Family history	●					
Medical history	●					
Drug allergy history	●					
Pre-trial medication*	●					
Vital signs	●		●	●	●	●
Physical examination	●			●	●	●
Laboratory examination						
Routine blood test	●		●	●	●	●
CRP	●			●	●	●
ESR	●			●	●	●
Routine urine/stool test	●			●	●	●
RF + ASO	●			●	●	●
Blood biochemical examination**	●		●	●	●	●
ACPA	●					●
Color Doppler ultrasound		●		●	●	●
Other laboratory results		●		●	●	●
Pre-RA diagnosis	●					
Evaluate RA conversion			●	●	●	●
TCM syndrome diagnosis	●					
Inclusion/exclusion criteria	●					
Screening results	●					
Sign informed consent form	●					
Evaluate disease activity (DAS28/PGA/CDAI/SDAI/VAS)		●		●	●	●
TCM symptom integral		●		●	●	●
Health Assessment Questionnaire-Disability Index		●				●
FACIT-Fatigue Scale		●				●
Suspension standards			●	●	●	●
Prescription		●	●	●	●	●
Combined drugs***		●	●			
Adverse event***		●	●	●	●	●
Distribution of medicine by express mail		●	●	●	●	●
End of study summary						●

*Record medications that were used and discontinued prior to the study. Drugs that were not discontinued prior to the study and entered the treatment period should be recorded in “Combined Drugs”. **Only liver function needs to be tested at 2 weeks. ***Observe continuously throughout the study and record when it occurs.

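### Survival time starts at consent rather than day 0, and RA status is not scheduled for recheck before treatment: untreated time enters the supplementary Kaplan-Meier analysis, and pre-treatment transitions count as trial events

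*Protocol article*

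**What the plan says.** All references are to the protocol article.

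- **Clock (section 2.6.1.1).** "Survival time will be recorded as the number of days between the date of informed consent and the date of transition".
- **Event (section 2.6.1.1).** "pre-RA patients who fulfill any criteria of RA classification at any time will be defined as" a transition. No lower limit at randomisation or day 0 is given.
- **Screening (Table 3, section 2.7).** The rows "Sign informed consent form" and "Pre-RA diagnosis", and the eligibility check, are ticked only in the column running from −4 weeks to day 0.
- **Day 0 (Table 3).** Prescription and delivery of medicine begin in the 0 ± 2 days column. The row "Evaluate disease activity (DAS28/PGA/CDAI/SDAI/VAS" and the ultrasound row are also ticked there.
- **Conversion (Table 3).** The row "Evaluate RA conversion" is ticked at weeks 4, 12, 24 and 48, not at day 0. The last visit is at "48 weeks ± 5 days".
- **Treatment (section 2.5).** "Treatment will continue for 48 weeks". This section labels week 0 as recruitment.
- **Safety follow-up (section 2.6.3).** Consent and enrolment are treated as one starting point for 48 weeks of monitoring.
- **Analysis (section 2.12.1).** The final transition rate is compared by chi-square or Fisher's test. Kaplan-Meier is added to that.

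**The concern.** There are two separate problems.

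**Time origin.** A patient who consents 4 weeks before day 0 reaches the week-48 visit at about day 364 on the consent clock; one who consents on day 0 reaches it at day 336. Assessments made at the same study time are spread over a month. RA-free patients with short gaps are censored before others reach the same visit, so late events fall on a shrinking risk set. The Kaplan-Meier curve may then disagree with the crude proportion for the same primary outcome.

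**No scheduled RA check at day 0.** A patient who crosses the RA criteria between screening and day 0 would be randomised, treated, found at week 4 at the earliest, and counted as a transition. Treatment cannot prevent such an event. It adds equally to both arms, so it dilutes the difference, and this reaches the chi-square test too.

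**Working it through.** **1. The plan's own figure.** Inputs from section 2.8: p1 = 0.5326, p2 = 0.70, two-sided alpha 0.05, power 0.90, unpooled Z-test.

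n = (1.960 + 1.282)² × [0.5326 × 0.4674 + 0.70 × 0.30] / (0.1674)² = 10.507 × 0.4589 / 0.02802 = 172.1, so 173 per group. Then 346 / 0.9 = 384.4, so 385. Both stated figures reproduce.

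**2. Hazards (constancy assumed).** Control: −ln(0.30)/52 = 0.02315 per week. YQCF: −ln(0.4674)/52 = 0.01463 per week. True week-48 rates: 1 − exp(−48 × 0.02315) = 67% and 1 − exp(−48 × 0.01463) = 50%.

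**3. Kaplan-Meier under different clocks.** Simulation with 195 per arm, no dropout, detection at days 28, 84, 168 and 336, RA-free completers censored at their last visit, gap from consent to day 0 uniform and unrelated to arm. Windows are those of Table 3 (± 2, 3, 5, 5 days). Entries are control/YQCF, approximate; the true values are 67%/50%.

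| Clock and dating | At day 336 | End of curve |
|---|---|---|
| Day 0, visits exactly on schedule | 67/50 | 67/50 |
| Consent, gap 0–7 days, visits on schedule | 46/32 | 85/71 |
| Consent, gap 0–28 days, visits on schedule | 44/30 | 91/80 |
| Day 0, visit windows | 58/44 | 87/74 |
| Consent, gap 0–28 days, visit windows | 44/31 | 94/85 |
| Consent, gap 0–28 days, exact transition dates | 65/49 | 69/52 |
| Day 0, visit windows, time in scheduled weeks | 67/50 | 67/50 |

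The day-336 reading has a simple check. On the consent clock almost nobody has had the week-48 visit by day 336, so the curve still shows roughly the week-24 rate: 1 − exp(−24 × 0.02315) = 43% and 1 − exp(−24 × 0.01463) = 30%.

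If a log-rank test accompanied the curves, simulated power (173 per arm, 70% and 53.26% reached by day 336) would be about 0.91 from day 0 with visits on schedule, 0.89 from day 0 with windows, and 0.86 from consent.

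**4. Transitions before day 0.** At the control hazard, a gap of g weeks gives q = 1 − exp(−0.02315 g). Each arm's rate becomes q + (1 − q)p, so the difference shrinks by the factor (1 − q). Power is Φ(difference / √{[p1(1 − p1) + p2(1 − p2)]/173} − 1.96), with the new rates for p1 and p2.

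| Gap | q | Of 390 | Difference (points) | Power |
|---|---|---|---|---|
| none | 0 | 0 | 16.7 | 0.90 |
| 1 week | 2.3% | about 9 | 16.4 | 0.89 |
| 2 weeks | 4.5% | about 18 | 16.0 | 0.88 |
| 4 weeks | 8.8% | about 34 | 15.3 | 0.85 |

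The last row needs every patient to wait the full 4 weeks. A uniform 0–28 day gap averages about 4.5%.

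**The case against.** A reader might infer that the consent clock by itself makes the transition rates badly wrong and undermines the primary result. The documents do not support that, for these reasons.

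- **The main comparison does not use the clock.** The chi-square or Fisher test is on the final proportion, and the trial is sized on two proportions. This stands.
- **The large error is conditional.** It needs visit dates used as transition dates, dates that are not tied, and a curve read at day 336 or at its tail. Section 2.6.1.1 says date of transition, not date of visit, and no reading time is given. With exact dates the error is 1–2 points. This stands, although the article describes no way to date a transition between visits, so visit dating is the likely practice.
- **Consent is not the only cause.** From day 0, the Table 3 windows alone give 58%/44% and then 87%/74%. Moving the origin without tying the visit times would leave much of the distortion. This stands.
- **Neither arm is favoured.** If randomisation is at day 0, the gap is unrelated to arm. This stands.
- **The gap may be short.** Sections 2.5 and 2.6.3 can be read as placing consent at or near enrolment, and Table 3 groups both pre-treatment columns under one visit. This stands as uncertainty about size. It also shows that the start date is described inconsistently.
- **A missing tick does not prove that a patient meeting RA criteria at day 0 would be enrolled.** True; but the event definition has no lower time limit, and nothing in the article stops such a patient being counted.
- **The dilution rate is probably high.** The 70% control rate refers to ACPA-positive patients. The trial also enrols anti-CCP-negative patients, whom section 4 describes as less likely to progress.

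**Conclusion.** The point holds as a moderate defect of definition, not as a fatal flaw. The time origin does not match the start of treatment or the visit schedule, and the sections disagree on when a patient's time begins.

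If visit dates are used, the supplementary Kaplan-Meier curve could differ from the crude week-48 rates by about 20 points or more in either direction. The screening gap and the week-48 window cause this together. If exact dates are available, the error is 1–2 points. The primary chi-square comparison is unaffected by the clock.

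The unscheduled day-0 check does affect that comparison, modestly: about 2–9% of patients for gaps of 1 to 4 weeks, alike in both arms, and roughly 1–5 points of power.

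These sizes rest on assumptions not in the documents: constant hazards, a uniform gap, randomisation at day 0, no dropout, and a pre-treatment hazard equal to the planned control rate. The last probably overstates the dilution in the mixed population.

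**What to change.** 1. Define survival time from randomisation, stated to be day 0, to the scheduled study week at which RA criteria are first met. Censor RA-free completers together at week 48. Alternatively, use an interval-censored method. Changing the origin alone is not enough.
2. Add an RA-criteria check to the 0 ± 2 days column of Table 3, before randomisation, using the disease activity assessment and ultrasound already scheduled there and the screening serology. Record patients who meet the criteria then as screen failures rather than transitions.
3. Reconcile sections 2.5, 2.6.1.1, 2.6.3 and Table 3 on the start date and on where consent falls.

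The cost is two sentences of wording and one tick in Table 3, with no new test. The downside is a few more screen failures. Settle the timing rule before unblinding. The day-0 check can help only patients not yet randomised.
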